### Participants and recruitment

#### Inclusion

In order to be eligible to participate in this study, a participant must meet the following criteria:
DSM- 5 BED or OSFED BED classification;age at least 18;BMI between 19.5 and 40;moderate proficiency in Dutch and ability to read part one of the Dutch translation of *Overcoming Binge Eating, The Proven Program to Learn Why You Binge and How You Can Stop*, by Christopher Fairburn [34], which involves psychoeducation;willingness to provide contact details, including phone number, internet access, possession of a computer or tablet, and willingness to use it for treatment and research purposes;willingness to sign the informed consent form.

#### Exclusion

Primary exclusion criteria are:
acute psychosis, assessed via Structural Clinical Interview by the DSM 5 (SCID-5) [35];acute depression, assessed via SCID-5;suicidal ideation, assessed via SCID-5 orself-induced vomiting as compensatory behavior, as reported at initial session or EDE-interview at baseline.having received eating disorder treatment during the past 6 months,being pregnantreported use of medication with the potential to influence eating behavior such as, Lithium, Mitrazepine and anti-psychotic stimulants [36, 37].

#### Recruitment

Recruitment will take place between September 2019 and December 2020. Potential participants will be referred to Novarum, center for eating disorders by other health care specialists. After being referred for specialized eating disorder treatment, potential participants have an initial screening consisting of an interview about eating disorders symptoms, other general psychiatric symptoms, life events and demographics. Weight and height will be measured in order to calculate their BMI. All eligible potential participants receive written study information during an advisory session, during which they receive an informed consent description, explaining the research goals and information about participation in the study. When willing to participate they sign the informed consent form and their baseline assessment will be planned. As an incentive for participating, participants will receive €10,- in gifts cards after completion of T2 (12 weeks), after completion of T3 (24 weeks) and €20,- after measurement at T4 (36 weeks). Participants who complete all follow-up questionnaires will thus receive a total amount of €40 in gifts cards as compensation for participating in the study.

### Intervention and procedure

All participants will receive GSH CBT-E: the experimental group will receive treatment immediately after baseline assessment, and the control group after a 12 weeks waiting period. GSH CBT-E is an online guided self-help version of CBT-Enhanced [8], based on *Overcoming Binge Eating, The Proven Program to Learn Why You Binge and How You Can Stop* [23], whose second part, a self-help guide, has been transformed into an online intervention.

#### Development of the intervention

The GSH CBT-E protocol was converted into an online program by CBT-Enhanced trained specialists at Novarum, center for eating disorders. A software team implemented the protocol on a website. During the pilot phase of the initial version, through an interactive process involving participants and therapists feedback, the website was further developed in terms of user friendliness, ease of navigation, lay-out and reduction in eating disorder pathology, measured by the Eating Disorder Examination-Questionnaire (EDE-Q) [29]. A risk inventory was performed [38] and GSH-CBT-E appeared to be a medical device involving minimal risks, therefore it was not necessary to gain permission with the Dutch Health Care Inspectorate [39].

#### Procedure

##### Therapists

Therapists activate an account and participants log into their digital environment through my.karify.com. Both categories have to register with a personal username and password. Both categories are able to access the intervention at any time. Once the patient completes an assignment, the therapist receives a notification by email and can access the assignments. All therapists are trained CBT-E therapists, successfully completed a web based CBT-Enhanced training provided by Centre for Research on Eating Disorders at Oxford (CREDO) and worked through the detailed CBT- Enhanced guide [8]. The therapists have different disciplinary backgrounds and have completed a post doc degree (mental health care psychologist), a masters degree (psychologist), or a bachelors degree (dietician and social worker). A manual explaining all intervention modules in detail is available to all GSH CBT-E therapists. After completing their CBT-Enhanced training by CREDO, all therapists received 2 days of training, including background information, program navigation, working with scripts, treatment content and communication skills. All therapists will receive supervision once a week, including general guidelines, discussion of adverse events and participants’ treatment progress. Therapists will not be blinded.

##### Intervention

GSH-CBT-E is based on Cognitive Behavioral Therapy- Enhanced, focused version, offered in a guided self-help format consisting of CBT-Enhanced key interventions, inevitably however less complex and with a shorter duration as in CBT-Enhanced focused. Before participants are eligible to start treatment, they have to read Part one of *Overcoming Binge Eating, The Proven Program to Learn Why You Binge and How You Can Stop* [23], or the Dutch translation *Overwin je eetbuien, waarom je te veel eet en hoe je daar mee kunt stoppen* [34]*.* This contains psycho-education about eating disorders and will be referred to during treatment. Participants will be asked if they have read part one before start of treatment. If the patient has not, they will be asked to read it during the first week(s) of treatment. In addition, before starting treatment, baseline assessment will take place. The EDE will be conducted by phone and participants will be sent a link to the self-report questionnaires, which they can complete at home on a computer. After baseline assessment and reading part one of *Overcoming Binge Eating The Proven Program to Learn Why You Binge and How You Can Stop* [23], the patient will be ready to start GSH CBT-E. Just like regular CBT-Enhanced, GSH CBT-E comprises three main stages; the first stage focuses on establishing regular eating and alternatives for binge-eating, using real-time self-monitoring as central intervention, and events, moods and eating. After joint review of progress & designing rest of treatment in the second stage, the third stages focuses on dietary restraint or shape concern and finally ending well with a firm focus on minimizing the risk of relapse in the long term. GSH CBT-E is a 12 week program. Once a week there will be a therapy session. All sessions will be conducted by phone. Participants have to start reading information online, to monitor their eating behavior, and to schedule, once a week, weighing, and, twice a week, self-evaluation sessions. The program is interactive, participants have to upload assignments and the therapist can monitor them. In addition, patient and therapist do interact weekly. Therefore, it differs from merely reading an e-book. A few days after start of treatment, participants will have a 20 min phone session with their therapist. To ensure consistency between therapists, these phone sessions are pre-scripted. During the first 4 weeks, participants will have to monitor their eating behavior, including their thoughts and feelings and establish a regular eating pattern. They will also introduce alternative activities for binge eating and work on problem-solving skills. During week 5, they will fill out assessment questionnaires, sent to them by a link, and their progress will be assessed, by both themselves and their therapist. This session will enable them to decide whether to add a module on body evaluation or dietary restraint during week 6–11 in addition to monitoring, regular eating, alternatives for binge eating and problem solving (Table 1). From week six onwards the program modifies to the user, based on the maintaining factors of their binge eating disorder. Before the 12th session participants will have to fill out the questionnaires. Results will be discussed during session 12, when they will also discuss what to do to prevent set-backs. The post treatment EDE will be conducted by phone. GSH CBT-E treatment will not be altered or interfered with during the study. As GSH CBT-E is a 100% guided self-help treatment without face to face sessions. After conclusion of the treatment, participants can still access the treatment module. To ensure data protection GSH- CBT-E is only available through a HTTPS protocol and secured by a 256-bit encrypted SSL- certificate. The online environment (Karify) is ISO 27001 and NEN 7510 certified.

**Table 1 Tab1:** Overview of timing of interventions in GSH CBT-E

Step	Focus	Period (12 weeks total)
Step 1	Starting well	1 week
Step 2	Establish a regular eating pattern	1 week
Step 3	Alternatives for binge eating	1 week
Step 4	Problem solving	1 week
Step 5	Evaluation	1 week
Step 6	Module: dietary restraint	Distributed over 6 weeks
Step 6	Module: shape concern	Distributed over 6 weeks
Step 8	Ending well	1 week

However, when another disorder than BED becomes the participants’ primary complaint and interferes with GSH CBT-E this will be considered as an adverse event. When the participant meets the criteria of Bulimia Nervosa instead of Binge Eating Disorder, as reported at the initial session or EDE-interview at baseline [40] the participant will no longer partake in the protocol and will be offered face to face treatment. In addition, patients will report on the frequency of their eating disorder behaviors on a weekly basis, monitored by their therapist. Although sessions are conducted by phone, all therapists will pay close attention to adverse events and patients will receive face-to-face treatment when dealing with adverse events. If presence of another psychiatric disorder interferes with GSH CBT-E, the participant will first consult a psychiatrist and receive face to face treatment or will be offered treatment in or outside our institutions.

##### Experimental treatment group

Participants assigned to the experimental condition will start their GSH CBT-E intervention directly after baseline assessment.

##### Waiting list control group

Participants assigned to the non- experimental (waiting list) condition will start their GSH CBT-E treatment 12 weeks after baseline. This control condition will be a minimal intervention. Participants will be called every 6 weeks for a short conversation (10 min at most), which will include checking on the eating disorder symptoms and other important areas of the participant’s life. This is necessary as, under Dutch law, monitoring participants during their waiting list period is mandatory at least every 6 weeks.

### Outcome measures and assessment

#### Outcome measures

##### Primary outcome measure

The primary outcome measure will be difference in eating disorder pathology, operationalized as the amount of days binge eating occurred, post treatment versus the waiting list control condition. Due to the absence of purging behavior, participants experience difficulty to recall the number of binge eating episodes. Therefore, participants suffering from BED were asked to report the number of days binge eating occurred rather than number of episodes [26, 41]. This is in line with the primary outcome measure chosen in another study [41]. Amount of binge free days will be measured by the EDE [28] and EDE-Q [29]. If a discrepancy arises between binge free days on the EDE and EDE-Q, the EDE will be chosen over the EDE-Q, because it is the golden standard for assessing eating disorder pathology [42].

##### Secondary outcome measure

As secondary outcomes, differences in other eating disorder pathology defined as restraint, eating concern, weight concern and shape concern [29, 40], quality of life and clinical impairment will be assessed. Eating disorder pathology will be measured by the EDE [28] and EDE-Q [29]. Quality of life will be measured by the five-level variant of the five-dimensional EuroQol instrument (EQ-5D- 5 L) [43]. Clinical impairment will be assessed through the Clinical Impairment Assessment (CIA) developed by Bohn et al. [44].

##### Costs

The economic evaluation will be performed in line with the ISPOR guidelines [45] and the Consolidated Health Economic Evaluation Reporting Standards (CHEERS) statement [46]. Several types of costs will be assessed: utilization of health care, costs stemming from productivity losses due to absenteeism or reduced efficiency while at work (presenteeism) and GSH CBT-E costs. Utilization of health care, other than for GSH CBT-E and utilization of health care within Arkin will be assessed by the questionnaire for Costs associated with Psychiatric Illness (TiC-P) [47]. Health care use will be multiplied with standard cost prices [48]. In addition, the participants electronic file will be searched to make additional calculations on costs other than GSH CBT-E within Arkin. Regarding productivity losses, we will use the Dutch guideline for economic evaluation [49], and rely on the standard cost prices reported therein. Productivity losses will be based on the gender- and age-specific friction costs. In addition, costs of GSH CBT-E (expressed in euros) will be established for each participant by multiplying standard Dutch cost prices [49], with the number of patient contacts. Since the time horizon of this study, mean time frame between start and end of treatment, is under a year, no discounting for future costs / effects will be applied.

##### Other study outcome measures

The variables that will be investigated as moderators of treatment effect are: therapeutic alliance, demographic variables, and the online module followed by the participant (dietary restraint or shape concern). Therapeutic alliance, hypothesized to be a moderator, will be measured through the Working Alliance Inventory (WAI) [50]. Gender is not expected to influence treatment outcome [27].

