**Methods:**

The efficacy of an online guided self-help intervention for binge eating disorder will be assessed by conducting a randomized controlled trial. The trial will target adult individuals classified with binge eating disorder or other specified feeding or eating disorder- binge eating disorder with a body mass index between 19.5 and 40, referred to an eating disorder treatment center. Dual arm allotment will be performed in a 1:1 ratio stratified for BMI above or below 30. Randomization will be blinded to the online intervention (*n* = 90), or to the control waiting list condition (*n* = 90). Assessors will be blinded and assessments will be administered at baseline, week 5, at end-of-treatment, and at 12 and 24 weeks follow-up. Primary outcome will be eating disorder pathology, operationalized as number of days on which binge eating occurred between the two conditions during the period of the intervention. Secondary outcome measures will be differences in other eating disorder pathology, clinical impairment and in quality of life, while therapeutic alliance, demographic characteristics and followed treatment module will serve as effect moderators. Several types of costs will be assessed.

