#### Assessment

All assessments will be conducted by phone (EDE) or via a link provided by e-mail (EDE-Q, CIA, EQ-5D-5 L, WAI). The EDE will be conducted at start (week 0) and post treatment (week 12). These assessments will be conducted by research assistants who will be blinded. If blinding is broken, the assessment will still be completed, and the results compared with results of the other participants in the same condition. If the results of the participant with broken blinding are outliers, they will not be taken into account in the analyses. All other assessments will be conducted at start, during week 5, week 12 and at week 24 and 36 (see also Figs. 1 and 2). Since treatment effect is expected to continue after end of treatment [11, 12], follow up measures will be conducted. If a participant does not complete the online assessments they will be called by a research assistant in order to motivate them. All assessments will be processed in Castor EDC (https://www.castoredc.com/) which is ISO 27001/27002/9001 and NEN 7510 certified. In addition, staff conducting the assessments do not offer GSH-CBT-E themselves.

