### Randomization

Randomization will take place after baseline assessment. Dual arm allocation will be performed in a 1:1 ratio, stratified for BMI score. Strata will be defined based on BMI: 19.5 ≥ BMI < 30 or 30 ≥ BMI < 40 by randomly selected block sizes of four, six and eight. Randomization will be performed digitally using Castor EDC (https://www.castoredc.com/) by an independent Arkin data processor not involved in this study. Participants will be informed about their allocation by email by the second author. All other authors will be blinded.

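### Therapeutic alliance and the module followed are named as moderators of treatment effect, but both arise after randomisation and neither exists in the waiting-list arm before the week-12 endpoint

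*Protocol article*

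**What the plan says.** The section Other study outcome measures of the protocol article says: "The variables that will be investigated as moderators of treatment effect are: therapeutic alliance, demographic variables, and the online module followed by the participant", the modules being dietary restraint and shape concern. For alliance it adds an explicit hypothesis: "Therapeutic alliance, hypothesized to be a moderator, will be measured through the Working Alliance Inventory (WAI"). The Methods paragraph of the abstract gives the same three roles: "therapeutic alliance, demographic characteristics and followed treatment module will serve as effect moderators".

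The article also fixes when each variable arises:

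- Under Randomization: "Randomization will take place after baseline assessment".
- Under Intervention, on the week-5 evaluation: "This session will enable them to decide whether to add a module on body evaluation or dietary restraint during week 6–11". Participant and therapist review progress in that week. From week six the programme is tailored to the factors that maintain the participant's disorder.
- Under Therapeutic Alliance (WAI), the instrument records the patient's view of the working alliance with the therapist.
- Under Waiting list control group, treatment starts 12 weeks after baseline. Until then the only contact described is a monitoring call of at most 10 minutes every 6 weeks.
- Under Statistical analysis, the primary endpoint is 12 weeks after randomisation.

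**The concern.** A moderator of a randomised treatment effect is a characteristic across whose levels the difference between arms varies. To study it, one must be able to classify participants in both arms by it, and the classification must not be a consequence of the arm. Baseline demographics meet both conditions. Alliance with the treating therapist and the module followed meet neither, because they come into being through receiving the treatment.

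What is at stake is interpretation. The Background cites a stronger alliance as improving efficacy and prefers phone to e-mail contact partly on that ground, so a result on alliance is likely to be read with interest. Participants who were going to do well may also rate the alliance higher. If that pattern is reported under the label moderator, it reads as evidence that alliance changes how well GSH CBT-E works against waiting list, and this design cannot show that.

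**Working it through.** **Plan's own figures.** The article gives no figure for any moderator analysis. Its sample size is for the main effect, and it reproduces: 2 × (1.960 + 0.842)² / 0.47² = 71.1, so 72 per arm (72.04 by the t-test, power 0.80 at 72). The planned number after the drop-out allowance is 90 per arm.

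**Step 1: timing, in weeks since randomisation.**

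| | GSH CBT-E arm | Waiting-list arm |
|---|---|---|
| Treatment starts | about week 0 | week 12 |
| Alliance with therapist can form | from start of treatment | after week 12 |
| Module decided (treatment week 5) | about week 5 | about 12 + 5 = week 17 |
| Primary endpoint | week 12 | week 12 |
| Participants who can have either value before the endpoint | up to 90 of 90 | 0 of 90 |

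Both variables come after randomisation in both arms. In the waiting-list arm they also come after the endpoint.

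**Step 2: can the interaction be estimated?** Let A be arm (1 = GSH CBT-E, 0 = waiting list) and M the alliance score or module. The usual moderator model is

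E(Y) = b0 + b1·A + b2·M + b3·A·M,

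with b3 as the moderation. In the waiting-list arm M has no value.

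- If M is left missing there, all waiting-list rows drop out and no comparison between arms remains.
- If M is set to any constant c there, then M = c − c·A + A·M for every participant. The M column is an exact combination of the other three, the design matrix has rank 3 of 4, and b2 and b3 cannot be separated. This does not depend on the choice of c.
- If the waiting-list arm's later values (weeks 12 to 24) are carried back, participants are classified by something recorded after, and possibly affected by, their week-12 outcome.

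Only the association of M with outcome among treated participants can be estimated.

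**Step 3: how that association can mislead (illustration on assumed values).** Suppose there is no moderation: everyone gains exactly 0.47 SD. Let U be poor prognosis, with correlation 0.5 with the outcome, and let alliance correlate −r with U. Splitting treated participants at the median alliance, the mean of U in the high half is −r·√(2/π) = −0.798r. Then

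- high alliance against waiting list: −0.47 − 0.5 × 0.798r = −0.47 − 0.399r
- low alliance against waiting list: −0.47 + 0.399r

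| r (assumed) | High alliance | Low alliance | Apparent difference |
|---|---|---|---|
| 0.2 | −0.55 | −0.39 | 0.16 |
| 0.3 | −0.59 | −0.35 | 0.24 |
| 0.5 | −0.67 | −0.27 | 0.40 |

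Simulating the same model gives the same arm contrasts to two decimals. A difference appears although the true effect is constant. The correlations are assumptions, since the article gives none.

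**The case against.** The strongest reply is that the article specifies no arm-by-alliance or arm-by-module term and does not tie the moderator question to week 12. It devotes a few sentences to it under other outcomes, and the modelling may be left to an analysis plan that is not shown. That is fair as to the model. It does not rescue the label: the text says moderators of treatment effect, hypothesises this role for alliance, and nowhere limits it to treated participants. The obstacle is in the design, so further detail cannot remove it.

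A second reply is that everyone eventually receives GSH CBT-E, so alliance and module can be related to change under treatment in up to 180 participants. This stands, and it means the data are useful. But once both arms are treated no untreated comparison remains, so the result is still prediction and not moderation of the randomised contrast.

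A third reply is that the choice of module need not reflect early response. This also stands in part. The stated basis for tailoring is maintaining factors, with progress reviewed in the same week. The safe statement is that module choice is not randomised and may reflect prognosis, maintaining factors or progress.

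**Conclusion.** The point holds as a matter of timing and needs no assumed figure. Moderation of the GSH CBT-E versus waiting-list effect by alliance or by module cannot be estimated, because 0 of 90 planned waiting-list participants can have either value before week 12. The sizes in step 3 are an illustration and rest on assumed correlations. The matter is of moderate weight: the primary and secondary comparisons, randomisation and sample size are untouched, and demographic variables remain legitimate moderators.

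Three stronger readings are tempting and not supported:

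- That the alliance questionnaire is wrongly scheduled before any therapy. The Assessment section does say "All other assessments will be conducted at start, during week 5, week 12 and at week 24 and 36", but this is a general sentence that refers to figures not shown. Demographics, for example, are taken at baseline only, so not every measure follows it.
- That module choice is driven by early response. The article names maintaining factors.
- That the trial will publish a causal subgroup claim. Nothing in the article announces one; the fault is in the role assigned to the two variables.

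**What to change.** In the abstract's Methods and in Other study outcome measures:

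- Limit moderator (arm-by-covariate) tests to baseline demographic variables.
- Reclassify alliance and module as exploratory predictors of outcome among participants receiving GSH CBT-E, and state that these associations are non-randomised and will not be reported as effect moderation.
- Adjust them for baseline and week-5 binge days, and name the EDE-Q as the source, since the EDE interview is taken only at weeks 0 and 12. This adjustment does not remove confounding by the maintaining factors behind module choice, so the word exploratory is needed even after it.
- Optionally add the waiting-list arm's own treatment period (weeks 12 to 24) as uncontrolled data. The outcome there would have to be the EDE-Q, because the text schedules no EDE at week 24. The text also lists no study assessment near week 17, so whether mid-treatment values exist for this arm should be checked first.

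The cost is a few reworded sentences and the loss of the moderation claim for alliance and module. The week-5 EDE-Q is already scheduled. Randomisation, sample size, treatment and the primary analysis do not change.
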